## Abstract

**Introduction:**

Diabetes affects ~10% of the world’s population and is rising. Treatment costs in the UK are ~15% of the NHS budget. Diabetes-related complications can be lowered through better evidence-based clinician management and patient self-management. MyWay intelligence quotient (MWIQ) is an electronic platform that will provide clinical decision support around the diagnosis and treatment of patients with diabetes. This study evaluates the safety and clinical performance (clinical appropriateness/applicability, clinical impact and clinical usability) of MWIQ.

**Methods and analysis:**

The system will be implemented in real time in four to seven general practitioner (GP) practices. Clinicians with diabetes expertise will be recruited as validators, who will inspect records to ensure system robustness before use, and up to 14 healthcare professionals will use and evaluate the system.

Quantitative and qualitative analyses will be triangulated to assess the MWIQ system. Assessment of clinical outcomes will be made using pseudonymised routinely collected clinical data, including adherence to quality performance indicators, diabetes diagnosis, diabetes investigations (eg, genetic testing), HbA1c, blood pressure, body mass index, cholesterol and foot risk score for the diabetes population concerned. Clinical and validator participants will also submit a weekly questionnaire, and these, along with interviews, which are scheduled during the testing process, will be analysed to provide data on the utility, safety and usability of the system.

**Ethics and dissemination:**

This study was approved, 08/01/2024, by the North of Scotland Research Ethics Committee (REC), IRAS project ID: 305267, REC, reference 23/NS/0134. The study has gained confidentiality advisory group (CAG) support (reference: 24/CAG/0002), medicines and healthcare products regulatory agency (MHRA) and health research authority (27/08/2024) approvals.

Findings will be reported to (1) The funding body, (2) The participating GP practices, (3) The study PPIE group, (4) The MHRA to support a submission for recognition as a class 2 CE/UKCA marked device, (5) Presented at local, national and international conferences and (6) Disseminated by peer-reviewed publications.

**Trial registration number:**

ISRCTN17422256.

STRENGTHS AND LIMITATIONS OF THIS STUDYTesting in ‘real-world’ circumstances ensures that clinician participant feedback is representative of system usage within a normal, busy clinical context, making results more generalisable.Similarly, the involvement of multiple primary care centres will ensure that any findings are more generalisable to the wider primary care community.Using validators to mitigate potential risks strengthens the testing framework.The quantitative analysis will be limited to providing descriptive statistics rather than statistical inference. These feasibility data will inform the design of future planned intervention studies.Any technical issues that develop during testing may shorten the length of time the system is tested.

## Introduction

 Diabetes affects ~10% of the world’s population and is rising. Treatment costs in the UK are ~15% of the NHS budget; 40% of which is spent on treating diabetes-related complications.^1 2^ The majority of these complications are preventable through better clinician evidence-based management and patient self-management.^2^

Precision medicine approaches through digital clinical decision support systems (CDSS) have been shown to offer safe and effective ways to manage diabetes and are starting to demonstrate improvements in clinical outcomes,^3 4^ including improvements in key parameters such as HbA1c.^5^ These systems are also starting to prove cost-effective.^6^ In addition, the potential for providing patients with information for self-management is high.^7 8^ But as the American diabetes association/European association for the study of diabetes consensus report highlighted, more work is required in this area.^9^

A precision-medicine approach with automated clinical decision support lends itself well to diabetes, where diverse factors are taken into account when managing a condition.^10^ Key areas include precision diagnostics, therapeutics and prognostics.^8^ Diabetes diagnostic sub-typing is complex, with approximately 15% of people incorrectly classified,^11^ potentially leading to inappropriate, higher risk/costly medications (including unnecessary use of insulin injections) and a significant impact on quality of life. Underdiagnosed subtypes include: (1) Genetic types known as maturity onset diabetes of the young, (2) Latent onset autoimmune diabetes of adulthood and (3) Diabetes due to secondary causes. In addition, type 2 diabetes has multiple distinct phenotypes.^11 12^ Drug response is also highly dictated by phenotype and genotype,^13^ yet treatment protocols are not always tailored in this way, which continues the lack of personalisation of results and ineffective medications/polypharmacy.^14^ In addition, most patients are managed in primary care where specialist input may be limited and where complications risk factor management in diabetes is rarely optimised.^15 16^

This study will contribute to the evidence base for AI-driven digital CDSS in use for chronic disease management through the development and testing of MyWay intelligence quotient (MWIQ).

### MyWay intelligence quotient (MWIQ)

MWIQ V.1.1 is an online electronic platform that provides clinical decision support around the diagnosis and treatment of patients with diabetes and will be delivered as part of the MyWay clinical and MyWay diabetes patient-facing platforms. The MWIQ clinician interface tool contains ~70 predictive models, generated through machine learning techniques and developed by MyWay digital health (MWDH). These models will be operationalised to predict glycaemic/metabolic response to type 2 diabetes pharmacological treatments, diagnosis of rare diabetes subtypes and risk of diabetes-related complications. In addition, they will provide a clinical overview of patient populations.

MWIQ machine learning models were developed through validated literature-based models, then the development of meta-models derived from them and the creation of de-novo models.

The validated literature and meta-models development predict diabetes subtype, diabetes acute and a large range of chronic complications, including cardiovascular disease, renal complications, amputation, blindness, hypoglycaemia, hospitalisation, re-hospitalisation, mortality, etc, and response to lifestyle interventions. The drug response prediction uses multi-dimensional time series data to predict the likely response to defined medications (counterfactual conditions) in domains of interest (HbA1c, blood pressure (BP), etc). Predicted outcomes guide individual therapeutic choice.

MWIQ will provide clear guideline-linked evidence-based decision support, particularly helping primary care staff who may lack specialist knowledge, by building on basic rule-based decision support, which has previously been shown to improve compliance with the guidelines by around 3–4 fold.^17^ Another important feature of the MWIQ system is the human factors approach, which is built into the development and research from the start.^18^

MWIQ aims to improve adherence to existing guidelines, while providing tailored treatment and diagnostic recommendations (within these existing guidelines) to improve future clinical outcomes (figures1  2). MWIQ is not intended to replace the care provided by licensed healthcare professionals (HCPs), involving prescribing, diagnosis or treatment. The system is supportive and advisory. Any treatment decision ultimately requires clinical judgement, taking the full clinical scenario into consideration.

**Figure 1 F1:**
[figure not shown]
The MyWay IQ clinician’s view for a (fictitious) patient. Includes data pertaining to body mass index (BMI); haemoglobin A1c (HbA1c); estimated glomerular filtration rate (eGFR); albumin to creatinine ratio (ACR).

**Figure 2 F2:**
[figure not shown]
MyWay IQ example of a (fictitious) medication recommendations panel. Takes into account presence or absence of cardiovascular disease (CVD); congestive heart failure (CHF); and cardiovascular risk score (QRisk2).

## Study aim

The study will use real-world environments to assess the clinical safety and performance of MWIQ. The primary objective is to iteratively test, identify and mitigate risks in the MWIQ system through a systematic evaluation of the platform’s safety in clinical settings. The secondary objectives are to evaluate the clinical performance of MWIQ measured in three areas: clinical appropriateness (applicability), clinical impact and clinical usability. A successful outcome will support a submission to MHRA for recognition as a class 2 CE/UKCA-marked device.

### Research question

Is the use of MWIQ safe, appropriate, usable and effective when used by primary care HCPs involved in the care of people with diabetes, in comparison to usual care?

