## Methods

### Study design

This study is an open-label, single-arm, mixed-methods feasibility testing of a support and decision-aid clinician-facing platform. Real-world testing will take place within the integrated care board, NHS Greater Manchester (the single site), with four to seven general practitioner (GP) surgeries participating across this large multicultural British city. The study contacted all practices within this area, and five practices responded positively. The study started recruitment for clinical participants on 28/08/2024. Live clinical testing started in March 2025, and the end of the study is 08/09/2025. Each participating practice serves a population of approximately 285 diabetes patients. Therefore, within the study period, it is anticipated that ~665 people with diabetes will attend their primary care practice for a diabetes check.

We will recruit one or two clinician participants from each of 5 GP practices, for a maximum of 10, to ensure the device is used in a variety of diabetes-related clinical settings and comprises a broad range of age groups, ethnicities and medical needs. Clinician participants will be members of the multidisciplinary team (GPs, specialist registered nurses (RNs) and advanced nurse prescribers who regularly see people with diabetes as part of their day-to-day work. They will provide a real-world perspective on how well the system integrates within the normal clinical workflow and provide feedback on how well the system performs. Sample size is calculated to withstand a small number of dropouts, while being large enough to draw out user views with different qualitative and quantitative methods and detect any safety issues across the long term. Each clinician participant will be invited to interview across the testing period (up to a maximum of 10 interviews). This is based on the narrow and focused scope of the interviews, collecting rich interview data by continuous interviewing throughout the study and the variety of HCPs involved in diabetes care in the primary sector and the anticipated number to reach data saturation for this type of study.

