Clinical impact	Routinely collected clinical data System navigation data Weekly questionnaire data	Number of patients with the following care processes recorded within the past 12 months: HbA1c, blood pressure (BP), serum cholesterol, serum creatinine, urinary albumin, foot screening, body mass index and smoking status. Each will be expressed as a percentage of the total number of people with diabetes seen by participants within the study period (and binomial proportion CI). Analysis will be stratified in accordance with diabetes type, age, gender, ethnicity and socioeconomic status (derived via the English index of multiple deprivation score) Number of patients meeting the following treatment targets: HbA1c <58 mmol/mol, BP=<140/80 mm Hg, Cholesterol <5 mmol/L, as well as the number meeting all three targets. Each will be expressed as a percentage of the total number of people with diabetes seen by participants within the study period (and binomial proportion CI) Number of patients with reclassified diabetes diagnosis, expressed as a percentage of the total number of people with diabetes seen by participants within the study period (and binomial proportion CI) and calculated on a monthly basis to demonstrate secular trends (if any) Number of patients with a modification in number of/dose/type of diabetes-related prescriptions (ie, insulin, metformin, DPP-4 inhibitors, pioglitazone, sulphonylurea and/or SLGT2-inhibitors) expressed as a percentage of the total number of people with diabetes seen by participants within the study period, calculated on a monthly basis to demonstrate secular trends (if any). Subjective assessment of system impact—recorded via a 5-point Likert scale. The distribution of scores will be expressed as a percentage of responses received Free-text comments submitted via questionnaire were analysed for emergent themes Number of participant interactions with the system, time spent within the system (cumulative total and per patient)
System appropriateness/applicability	Weekly questionnaires Semi-structured interviews	Clinical usefulness score recorded within weekly questionnaire for each of the MWIQ features (diabetes subtype predictor, diabetes drug response predictor and diabetes complications predictor) as well as overall experience. The score will be recorded via a 5-point Likert scale, and the distribution of scores will be expressed as a percentage of responses received Free-text comments will be analysed for emergent themes

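### The question of effectiveness against usual care has no usual-care reference in a single-arm, descriptive study, so that part of the research question cannot be answered

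*Protocol article*

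**What the plan says.** All references are to the protocol article.

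- **Research question.** It covers safety, appropriateness and usability, and also asks whether MWIQ is "effective when used by primary care HCPs involved in the care of people with diabetes, in comparison to usual care".
- **Study design.** "This study is an open-label, single-arm, mixed-methods feasibility testing of a support and decision-aid clinician-facing platform".
- **Strengths and limitations.** "The quantitative analysis will be limited to providing descriptive statistics rather than statistical inference", followed by "These feasibility data will inform the design of future planned intervention studies".
- **Table 2, Clinical impact.** Four measures come from patient records: "Number of patients with the following care processes recorded within the past 12 months"; "Number of patients meeting the following treatment targets"; reclassified diabetes diagnosis; and modified diabetes prescriptions. All four use people with diabetes seen by participants in the study period as denominator. The treatment-target entry, for example, reads "expressed as a percentage of the total number of people with diabetes seen by participants within the study period (and binomial proportion CI"). Reclassification and prescription changes are also "calculated on a monthly basis to demonstrate secular trends (if any").
- **Study aim.** Safety is the primary objective. Appropriateness, impact and usability are secondary. Neither effectiveness nor usual care is mentioned.
- **Analysis.** The one comparison named is between sources of data: participants' reports, researchers' observations and routine records.

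**The concern.** A descriptive study can describe a comparison, but it needs something to compare with. Care processes are recorded, targets are met, diagnoses are revised and prescriptions are changed in ordinary care too. A percentage observed while MWIQ is in use therefore does not show what MWIQ added.

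The results are meant to support a submission to the MHRA, and the full study title given under Ethics and dissemination speaks of safety and efficacy testing. If the percentages are reported under a question about effectiveness against usual care, a reader may take a level for an effect. The confidence intervals attached to three of the four measures could strengthen that impression.

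**Working it through.** **Step 1: look for a reference in each patient-level measure.**

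| Table 2 measure | Time element stated | Separate usual-care reference |
|---|---|---|
| Care processes | 12-month look-back, one percentage | None; no split at go-live |
| Treatment targets | Study period | None |
| Reclassified diagnosis | Study period, monthly | None; no months before go-live named |
| Prescription changes | Study period, monthly | None; no months before go-live named |

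No control practices, period before go-live, external benchmark or change from baseline is named. The remaining impact measures (Likert rating, free text, interaction counts, time in system) concern use of MWIQ itself and have no usual-care counterpart.

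**Step 2: can the look-back serve as a baseline?** Live testing began on an unstated day in March 2025 and ends on 8 September 2025, so it lasts D = 161 to 191 days.

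- If the look-back ends at each visit and visits are spread evenly (assumptions), the average share of the window before go-live is 1 − (D/2)/365. This gives 1 − 95.5/365 = 74% to 1 − 80.5/365 = 78%.
- If it ends at study end instead, the share is 1 − D/365. This gives 1 − 191/365 = 48% to 1 − 161/365 = 56%.

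Either way the percentage blends usual-care and MWIQ time. It is not a separate baseline.

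**Step 3: can the monthly figures serve?** They cover two of the four measures. The Analysis section has issues reviewed weekly and the system improved iteratively, so a trend over the test months mixes calendar time with changes to the system. No month without MWIQ is specified as a starting point.

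**Step 4: what the numbers can deliver.** The only patient number given is ~665 attending for a check. Five practices × 285 = 1,425 registered patients. At one check a year (assumption), 1,425 × 161/365 = 629 and 1,425 × 191/365 = 746. The stated figure lies in that range and is matched at 5.6 months (1,425 × 5.6/12 = 665). It is compatible, but cannot be reproduced strictly without the start day and visit rate.

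The 95% half-width of one percentage is 1.96 × √(p(1−p)/n), ignoring clustering by practice and clinician:

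- n = 665: 2.3 points at p = 0.1 and 3.8 points at p = 0.5 (assumed p).
- n ≈ 665/6 ≈ 111 a month: 5.6 to 9.3 points.

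These describe how well a level is known. As an assumed illustration, 20% with a prescription change is +10 points if the usual rate is 10%, 0 if it is 20%, and −5 if it is 25%. Nothing in the stated measures separates these cases, however narrow the interval.

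**The case against.** The strongest reply is that this is one clause in an otherwise modest document. The objectives contain no comparison, the design is called feasibility testing, the limitations rule out inference, and no decision rule depends on usual care; the monitoring board considers safety data. That is correct, and it lowers the severity. It does not withdraw the clause: the limitations give up inference, but do not say that a comparator is absent.

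Several stronger readings are tempting, and the documents do not support them.

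- A reader might infer that the whole research question fails. It does not: safety, appropriateness and usability have their own measures in Tables 1 and 2.
- A reader might infer that every impact measure is a single during-study percentage and that no usual-care time enters. The look-back reaches before go-live, two measures are monthly, and interaction counts and time in system are not percentages.
- A reader might infer that an effect claim to the MHRA is planned. The article says only that a successful outcome will support a submission.

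Reclassification and prescription changes are changes from a patient's earlier status, so they are not bare snapshots. What is missing is how often they occur without MWIQ.

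Finally, the article condenses a full protocol (V.5), which may define a reference period. The mismatch between the published question and the published measures stands regardless, because the article states both.

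**Conclusion.** The point holds for the comparative effectiveness part of the question only. As published, a single-arm, descriptive design with no separate usual-care reference in any of the four patient-level measures cannot show whether MWIQ is effective compared with usual care. Patient numbers do not cure this, since the planned intervals concern levels.

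The conclusion rests on reading the sections together. It does not depend on the assumed visit rate, proportions or look-back anchor, which serve only to show size. Severity is moderate: the correction changes what the study may conclude, but no outcome, safety rule or other objective is undermined.

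**What to change.** **Main change.** Reword the Research question to match the Study aim by removing effectiveness and the reference to usual care. Add a sentence to Table 2 or the Analysis section stating that the clinical-impact percentages are levels observed during use of MWIQ, not effects. This is a wording change with no operational cost.

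**If the comparison is kept.** Compute the four routine-record measures, and only those, for the same practices in the matching calendar months before go-live (March to 8 September 2024). Where possible restrict to patients seen by the same participating clinicians, because Table 2 counts people seen by participants; using everyone who had a check would mix clinician with period. Report the before-after difference descriptively and label it as uncontrolled.

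**Cost and limits of the second option.**

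- It needs a longer extract and a check that the confidentiality advisory group support and the available record history cover it. The 12-month look-back for 2024 visits would reach into 2023.
- With 665 people in each period, treated as independent and unclustered (assumptions), the half-width of a difference is √2 times that of one percentage: √2 × 2.28 = 3.2 to √2 × 3.80 = 5.4 points. It is wider if participating clinicians see fewer than 665.
- The result remains non-causal, since other changes between the two years cannot be separated from MWIQ.

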## Methods

### Study design

This study is an open-label, single-arm, mixed-methods feasibility testing of a support and decision-aid clinician-facing platform. Real-world testing will take place within the integrated care board, NHS Greater Manchester (the single site), with four to seven general practitioner (GP) surgeries participating across this large multicultural British city. The study contacted all practices within this area, and five practices responded positively. The study started recruitment for clinical participants on 28/08/2024. Live clinical testing started in March 2025, and the end of the study is 08/09/2025. Each participating practice serves a population of approximately 285 diabetes patients. Therefore, within the study period, it is anticipated that ~665 people with diabetes will attend their primary care practice for a diabetes check.

We will recruit one or two clinician participants from each of 5 GP practices, for a maximum of 10, to ensure the device is used in a variety of diabetes-related clinical settings and comprises a broad range of age groups, ethnicities and medical needs. Clinician participants will be members of the multidisciplinary team (GPs, specialist registered nurses (RNs) and advanced nurse prescribers who regularly see people with diabetes as part of their day-to-day work. They will provide a real-world perspective on how well the system integrates within the normal clinical workflow and provide feedback on how well the system performs. Sample size is calculated to withstand a small number of dropouts, while being large enough to draw out user views with different qualitative and quantitative methods and detect any safety issues across the long term. Each clinician participant will be invited to interview across the testing period (up to a maximum of 10 interviews). This is based on the narrow and focused scope of the interviews, collecting rich interview data by continuous interviewing throughout the study and the variety of HCPs involved in diabetes care in the primary sector and the anticipated number to reach data saturation for this type of study.

In addition, four validator participants will be recruited to review the patient data for safety issues. The validator participants will review the case records of all people with diabetes registered within the participating practice in advance of (and following) a scheduled diabetes review in the participating practice. Validation will consider the safety, applicability and usefulness of the system outputs. Any safety concerns will be flagged and investigated, and clinical participants will be advised not to access the patient record until the issue is resolved. Confidential advisory group approval has been granted to enable clinical validators to access relevant patient records in the participating clinics.

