### Qualitative data collection

Qualitative data will be gathered from free-text sections of the weekly questionnaires. Clinician participants will be invited for a semi-structured online interview to discuss the complexity of using the system in situ. Interviews will be 30–45 mins long and explore questions about what worked well and not-so-well in practice; which features were most useful, consultation flow when using the system, sharing screens with patients and using the system collaboratively with colleagues, safety, trust and what would make the system better. We will conduct interviews regularly throughout the testing phase and ask to interview all the participating clinician participants twice during this time, if possible.

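### The sample size cannot give the safety detection the protocol claims for it, and the clinician and interview maxima need reconciling

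*Protocol article*

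**What the plan says.** All references are to the protocol article.

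- **Detection claim.** Study design says the sample size is calculated to tolerate a few dropouts, to bring out users' views and to "detect any safety issues across the long term". It gives no event rate, confidence level or follow-up time. The sentence comes directly after the clinician recruitment target.
- **Clinicians and practices.** Study design: "We will recruit one or two clinician participants from each of 5 GP practices, for a maximum of 10". The same section describes the study "with four to seven general practitioner (GP) surgeries participating" and reports that "five practices responded positively". The abstract (Methods and analysis) says "up to 14 healthcare professionals will use and evaluate the system".
- **Patients.** Study design gives about 285 people with diabetes per practice, and for the study period "it is anticipated that ~665 people with diabetes will attend their primary care practice for a diabetes check".
- **Duration.** Study design has live testing starting in March 2025 and the study ending on 8 September 2025.
- **Interviews.** Study design allows "up to a maximum of 10 interviews". Qualitative data collection says the team will "ask to interview all the participating clinician participants twice during this time, if possible".
- **Denominators.** In Table 1 the primary safety percentage is based on records reviewed, with a binomial confidence interval. In Table 2 most clinical impact percentages are based on people seen by participants.

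**The concern.** The sentence attributes a statistical property to the sample. Taken literally, it promises that any safety issue, however rare or late, would be found. Safety is the primary outcome, and the Study aim section says a successful result will support a class 2 device submission. A report of few or no issues would then be read against a detection ability that the study lacks.

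The word long-term is also hard to reconcile with the tool. The section describing MWIQ lists predictions of chronic outcomes such as amputation, blindness, renal disease and death. Harm from a wrong prediction of that kind would mostly appear after a study of this length has closed.

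The clinician and interview counts matter less for inference. They do decide how much user evidence is collected, and Study design justifies the interview maximum by data saturation, so the maximum should match what participants are asked to do.

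**Working it through.** **1. The plan's own patient figure.** Inputs from Study design: 5 practices, 285 patients each, a start between 1 and 31 March 2025, and an end on 8 September 2025. Assumption: one diabetes check per patient per year (no attendance rate is stated).

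- Live window: 161 to 191 days, or 5.3 to 6.3 months.
- 5 × 285 = 1,425. Then 1,425 × 161/365 = 629 and 1,425 × 191/365 = 746.
- 665 / 1,425 = 0.467 of a year, or 5.6 months.

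The stated 665 lies inside 629 to 746, so it is reproduced.

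**2. Formulas.** For n independent units and a true frequency p, the chance of seeing at least one case is 1 − (1 − p)^n. The smallest p with a 95% chance of being seen is 1 − 0.05^(1/n).

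**3. Clinicians as the sample, as the sentence reads in context.**

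| Clinicians | Smallest share affected for 95% detection |
|---|---|
| 5 (one per practice) | 45.1% |
| 10 (Study design maximum) | 25.9% |
| 14 (abstract maximum) | 19.3% |

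An issue that 1 clinician in 10 would meet has a 1 − 0.9^10 = 65% chance of appearing among 10.

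**4. Patients as the sample, the most favourable reading.** Assume all 665 attendees are reviewed and independent.

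- Smallest rate for 95% detection: 1 − 0.05^(1/665) = 0.45%, about 1 in 222.

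| True rate per patient | Chance of at least one case, n = 665 | Records needed for 95% |
|---|---|---|
| 1% | 99.9% | 299 |
| 0.5% | 96.4% | 598 |
| 0.2% | 73.6% | 1,497 |
| 0.1% | 48.6% | 2,995 |
| 0.01% | 6.4% | 29,956 |

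**5. Why 0.45% is a best case.**

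- *Fewer records.* Patients may opt out. The reviewed records are also described in two ways: those of all registered people with a scheduled review (Study design), and those of each person the clinician participants see (Ensuring safety during testing). With 333 records (assumed) the threshold is 0.90%, and with 200 (assumed) it is 1.49%.
- *Clustering.* With 665/5 = 133 records per practice and an assumed intraclass correlation of 0.01, the design effect is 1 + 132 × 0.01 = 2.32. The effective n is 665/2.32 = 287, and the threshold is about 1.0%.

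**6. Counts side by side.**

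- *Clinicians.* 5 × 2 = 10 matches Study design. The abstract's 14 could be 7 × 2 or 10 clinicians plus 4 validators. The article does not say which, and the abstract names the validators separately.
- *Interviews at two each.* 5 clinicians give 10, 10 give 20 and 14 give 28, against a maximum of 10. The two statements agree only with five clinicians or fewer. With 6 to 9 clinicians all interviewed once, the maximum leaves room for 4 down to 1 second interviews. With 10 it leaves none.

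**The case against.** The strongest reply is that the sentence concerns clinicians. It sits between clinician recruitment and clinician interviews, the article says patients are not participants, and the 665 is a separate attendance forecast. That is right, and it means the patient-level calculation tests a more generous reading than the text makes. The claim still fails: on the clinician reading the threshold is about 26%, not 0.45%.

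A second reply is that the analysis is declared descriptive, the primary proportion carries a confidence interval, and validators, monthly safety board review and an urgent reporting route are in place. These stand as protections. They help an issue that occurs to be noticed and reported. They add neither patients nor follow-up time, and they do not make the sample size statement true.

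On the counts, the second interview is asked for only if possible, and 14 may be a planning ceiling for seven practices. Both points soften the mismatch. Neither is explained in the text. It would also go too far to say that the interview maximum must leave half the clinicians uninterviewed or nobody interviewed twice, since mixtures fit within it.

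A reader might further infer that 665 is miscalculated, that it conflicts with the Table 2 denominator of people seen by participants, or that every percentage rests on an overstated denominator. The article does not support any of these:

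- 665 is within the range implied by five practices and the stated dates. Other combinations (4 practices × 7 months, 7 × 4) also give 665, but that says nothing certain about its origin.
- Attendees and people seen by participants are different quantities, and the article never equates them.
- The primary measure divides by records reviewed and the Likert measures by responses received.

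**Conclusion.** The point holds for the detection claim. No sample in this study can find any safety issue over the long term. Observation is limited to about 5.3 to 6.3 months. Ten clinicians give 95% detection only of issues that about 26% or more of clinicians would meet. The most favourable patient reading needs a rate of about 0.45% or more, rising to about 1.0% under the assumed clustering. A 1-in-1,000 issue would be missed about as often as seen (49% seen). The clinician and patient figures assume independence, and the 0.45% also assumes that every expected attendee is reviewed.

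The interview and clinician maxima are real but minor mismatches: 10 against up to 20 interviews, and 10 against 14 clinicians. The design and the 665 forecast do not need to change on this account.

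**What to change.** 1. In Study design, delete the words any and across the long term. State the real limit instead, for example: *If N patient records are reviewed, an issue with a per-patient rate of at least 1 − 0.05^(1/N) has a 95% chance of being seen at least once during about six months of live use. This is a best case that assumes independent records; clustering within practices raises the rate.* N should be the expected number of records reviewed, stated explicitly and not taken to be all 665 attendees.
2. Reconcile the interview statements. Either raise the maximum to 20 for up to 10 clinicians, or keep 10 and say how second interviews will be limited.
3. Use one clinician maximum in the abstract and Study design. If 14 was a ceiling for seven practices or includes the validators, say so.

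The cost is wording, and a stated safety limit that looks less favourable than the present claim. Keeping both interview rounds adds up to 10 interviews of 30 to 45 minutes, or 5 to 7.5 hours of interview time.
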